### Power analysis

Power calculations were performed to further justify our proposed sample size. All of these assume a sample size of 1,800 per study arm, a significance level of 5% (*i.e.* alpha = 0.05), and a two-sided two-group chi-square test of proportions. Calculations were performed using nQuery Advisor, version 7. These are performed for hypothesis one (H1) and hypothesis three (H3); hypothesis two (H2) is qualitative, so power calculations do not apply. For H1, we anticipate that there will be 25%, 33%, and 50% greater participant enrollment with the Web + TA arm, IP arm, and IP + TA arm, respectively, when compared to the passive web-based-only arm (based on our prior experience with community coalition based studies). Comparisons of any of these proportions to any proportion that is obtained for the passive web-based arm (for example, 5%, 10%, or 20%) will result in greater than 99% power to detect differences in the proportions as being statistically significant. For H3, we can obtain estimates of cancer knowledge change over time (pre-intervention to post-intervention percentages with the correct response) for a small group education cohort and a control cohort from Blumenthal, Smith *et al.*[6]. These estimates include changes of 34.8 (71-36) and 15.5 (55.2-39) for a CRC perceived risk question, and 22.9 (92.9–70) and 13.1 (88.5–75.for a CRC screening question. Assuming that we observe similar changes in our study participants for active and passive arms, we will have greater than 99% power to detect differences in the proportions as being statistically significant.

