### Sample size calculation

We intend to enroll 7,200 individuals in this study, with 1,800 enrolled in each study arm. This sample size is based on 20 NBLIC community coalitions randomized to four study arms (WA, WA + TA, IP, IP + TA). There will also be three settings (church, clinic, and community site) per coalition. Each community coalition will have 30 groups of individuals completing three consecutive EPICS sessions, recruiting 15 individuals per setting with an expected 25% dropout rate; thus, we anticipate that 12 of these individuals will complete all three sessions. For the EPICS cRCT, there will be (30 groups of three sessions) × (12 individuals completing all three sessions) × (20 NBLIC community coalitions) = 7,200 individuals. Based on data from a previously published study, we calculated intracluster correlation coefficient (ICC) to equal 0.0911 (9.1%) [6]. The effective sample size (ESS) was 5,645, which still has high power (>99%) with design effect of 1.2754.

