### Primary outcome measures

The primary outcome for the EPICS cRCT focuses on the Reach and Effectiveness components of the RE-AIM (Reach, Effectiveness, Approach, Implementation, Maintenance) model. Reach refers to the proportion of representative eligible organizations, settings, and individuals participating in the intervention. To determine EPICS Reach, we will examine two dimensions of this concept, estimated based on the following calculation [24]:

Number of participants in

$$\text{Estimate}\;\text{of}\;\text{REACH}=\frac{\text{the}\;\text{target}\;\text{population}\;\text{who}\;\text{receive}\;\text{the}\;\text{three}\;\text{EPICS}\;\text{sessions}\;\times \;100}{\text{Number}\;\text{of}\;\text{eligible}\;\text{participants}\;\text{in}\;\text{the}\;\text{target}\;\text{settings}}$$

In the RE-AIM framework, effectiveness is the impact of the intervention on desired outcomes. For the EPICS cRCT, CRC screening adherence will be based on baseline community CRC screening rates from the Centers for Disease Control and Prevention’s (CDC) Behavioral Risk Factor Surveillance System (BRFSS), post intervention participant self-reported FOBT, flexible sigmoidoscopy and/or colonoscopy, and changes in facilitators’ CRC knowledge, attitudes, and beliefs. Adherence to CRC screening on a total population basis is calculated as:

Number of participants

$$\text{Adherence}\;\text{to}\;\text{CRC}\;\text{screening}=\frac{\text{adherent}\;\text{to}\;\text{CRC}\;\text{screening}\;\text{in}\;\text{the}\;\text{population}}{\text{Estimated}\;\text{target}\;\text{population}\;\text{by}\;\text{setting}}$$

In alignment with Glasgow’s RE-AIM definition, our estimate of effectiveness will be determined using the following formula [24]:

Number of participants in the sample of the target population

$$\text{Estimate}\;\text{of}\;\text{Effectiveness}=\frac{\text{who}\;\text{were}\;\text{Reached}\;\text{and}\;\text{adherent}\;\text{to}\;\text{CRC}\;\text{screening}}{\text{Number}\;\text{of}\;\text{participants}\;\text{in}\;\text{the}\;\text{target}\;\text{population}\;\text{who}\;\text{were}\;\text{reached}}$$

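### H1 is a single active-versus-passive contrast, but the Power analysis supports it with three unadjusted 5% comparisons against one web-only arm, one of which cannot test H1

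*Protocol article*

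**What the plan says.** All references are to the protocol article.

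- **Hypotheses.** H1 is one directional statement: active dissemination will enroll more participants than passive dissemination. The Abstract places both web arms, with and without TA, on the passive side and both in-person arms on the active side.
- **Sample size calculation.** The design is "20 NBLIC community coalitions randomized to four study arms (WA, WA + TA, IP, IP + TA"), and "We intend to enroll 7,200 individuals in this study, with 1,800 enrolled in each study arm".
- **Power analysis.** Of the calculations, the section says "All of these assume a sample size of 1,800 per study arm, a significance level of 5" percent, with a "two-sided two-group chi-square test of proportions". For H1 the anticipated effects are "25%, 33%, and 50% greater participant enrollment with the Web + TA arm, IP arm, and IP + TA arm", each relative to web-only. The section then states power above 99% for "Comparisons of any of these proportions to any proportion that is obtained for the passive web-based arm", with 5%, 10% and 20% as example web-only rates. These calculations cover H1 and H3 only.
- **Primary outcome measures.** "The primary outcome for the EPICS cRCT focuses on the Reach and Effectiveness components" of RE-AIM. The Abstract likewise lists reach and efficacy as primary. Neither place ranks them or says that both must succeed.
- **Effectiveness and the GEE model.** Screening rates are compared between passive and active approaches by setting, and inference in the GEE model rests on one interaction coefficient. No significance level is given for it.

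No adjustment for multiple comparisons is stated anywhere in this article.

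**The concern.** The hypothesis and the calculation that justifies the sample size describe different tests. H1 needs one contrast that pools two arms on each side. The Power analysis offers three contrasts that share one comparator. One of them, Web + TA against web-only, lies wholly within the passive group and says nothing about active against passive.

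Two things follow. First, the stated power is not the power of the test that H1 calls for. Second, the overall goal is to identify the most efficacious dissemination approach. If the three comparisons are the means of doing that, 5% is the error rate of each comparison and not of the conclusion. Having two unranked primary outcomes adds to this, because the article does not say whether success on one is enough.

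**Working it through.** **Inputs.** 1,800 per arm, equal allocation, two-sided 5%, three arms against web-only, effects of 25/33/50%, web-only rates of 5/10/20% (Sample size calculation and Power analysis). Clustering is ignored throughout, as in the article's H1 calculation; it is a separate matter.

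**1. The plan's own figure.** Power = Φ[(|p₁ − p₂| − 1.96·se₀)/se₁], with se₀ = √(2p̄(1 − p̄)/n), se₁ = √([p₁(1 − p₁) + p₂(1 − p₂)]/n) and n = 1,800.

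- If 25/33/50% are percentage points added to the web-only rate, all nine scenarios give about 100%. The stated figure of above 99% is reproduced.
- If they are relative increases, 5% against 6.25% gives se₀ = 0.00768, se₁ = 0.00768 and (0.0125 − 0.01505)/0.00768 = −0.33, so power is 37%. The full set is 37/56/87% (web-only 5%), 66/87/99.5% (10%) and 95/99.7/100% (20%). Three of nine exceed 99%.

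**2. Error over the three H1 comparisons.** With equal arms, two differences that share a comparator have correlation (1/n)/(2/n) = 0.5. If all arms are equal and c = 1.96:

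P(at least one |Z| > c) = 1 − ∫ φ(u)·[Φ((c − √0.5·u)/√0.5) − Φ((−c − √0.5·u)/√0.5)]³ du = **0.125**.

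- Counting only results that favour an enhanced arm: **0.063**.
- Treating the three tests as independent: 1 − 0.95³ = 0.143.
- Using t-tests on 16 degrees of freedom (20 coalitions − 4 arms): 0.121.
- The critical value that brings the two-sided error back to 0.05 is **2.349**, or 0.0188 per test.

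**3. Leaving out the comparison that cannot test H1.** For IP and IP + TA against web-only alone, the same integral with power 2 gives 0.091 in either direction and 0.045 in H1's direction.

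**4. Two primary outcomes, one active-versus-passive test each.** At an assumed 5% on each, 1 − 0.95² = 0.0975, or about **9.8%** if the outcomes are independent, and less if they are positively correlated. This ignores the split by setting. It also takes H1's enrollment as standing for Reach, which the article defines through completion of the three sessions.

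**5. Power of the contrast that H1 names.** With 3,600 per side, each group rate is the mean of its two arms. On the relative reading, passive = (p + 1.25p)/2 and active = (1.33p + 1.50p)/2.

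| Web-only rate | Passive | Active | Power at 5% | Power at 2.5% |
|---|---|---|---|---|
| 5% | 5.6% | 7.1% | 71% | 61% |
| 10% | 11.3% | 14.2% | 96% | 93% |
| 20% | 22.5% | 28.3% | >99.9% | >99.9% |

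On the percentage-point reading, power is about 100% in every row at either level.

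**6. Power of the three comparisons at the Dunnett level (0.0188).** On the relative reading: 24/41/77%, 51/77/99% and 89/99/100% for web-only rates of 5, 10 and 20%. On the percentage-point reading: about 100% throughout.

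**The case against.** The strongest reply is that the 5% is an input to a power calculation and not a testing procedure, and that multiplicity rules are commonly left to an analysis plan or full protocol that is not shown. This stands in part. The absence of an adjustment is not a fault in itself, and all that can be said is that none is stated in this article. It does not remove the mismatch, because H1 and the contrasts powered for it both stand in the article and differ.

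A second reply is that H1 is already one contrast and directional. Among the two comparisons that could bear on it, a false result in its direction has probability 4.5%. That is correct, but the Power analysis uses three two-sided comparisons. With four strategies under study, a false result favouring web-only would also mislead the choice among them.

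A reader might go further than the text allows in three ways:

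- One might apply the three comparisons to both primary outcomes and obtain about 24% over six tests (1 − 0.875² = 0.235 with independent outcomes). The article does not set this up. The 5% calculations cover H1 and H3, screening is compared between passive and active approaches, and the GEE inference has one coefficient with no stated level.
- One might read the wording about comparing any of the proportions as a rule that any one significant result is a success. It describes the range of power scenarios.
- One might call 12.5% the chance of a false win for an enhanced strategy. It counts both directions; the favourable part is about 6%.

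**Conclusion.** The point holds as an internal contradiction with a moderate consequence. H1 is one active-versus-passive contrast, while its power rests on three comparisons with web-only, one of them between two passive arms. If those three carry the conclusion, the error is about 12.5% in either direction, or about 6% in favour of an enhanced arm, instead of 5%. This assumes equal arms, normal test statistics and valid standard errors. With one active-versus-passive test on each of the two unranked primary outcomes, at an assumed 5%, the error is at most about 9.8% under independence. The documents do not support a figure near 24%, nor the statement that the trial has no error control. They support only that this article states none.

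**What to change.** In the Power analysis section:

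1. Name active (IP, IP + TA) against passive (WA, WA + TA) as the primary test of H1, and restate power for that contrast. Say whether 25/33/50% are relative increases or percentage points, since the answer depends on it.
2. State how Reach and Effectiveness are tested together: in a fixed order, or with Holm (smaller p-value at 2.5%, then the other at 5%).
3. Make the three comparisons with web-only secondary. If they are used to name a best strategy, apply Dunnett's adjustment (critical value about 2.35 in place of 1.96).

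The change is to wording only; design and enrollment stay as they are. The cost is slightly lower power for some tests. For the H1 contrast at 2.5% instead of 5%, power on the relative reading falls from 71% to 61% at a web-only rate of 5% and from 96% to 93% at 10%. It is essentially unchanged at 20%, and on the percentage-point reading throughout. These figures ignore clustering, so the restated power should be computed with clustering included.

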### Theoretical framework

We will use Rogers’ Diffusion of Innovation Theory and Glasgow’s RE-AIM (Reach, Effectiveness, Adoption, Implementation, Maintenance) evaluation framework to guide the EPICS cRCT (Figure 2).

**Figure 2 F2:**
[figure not shown]
Study overview.

Based on Rogers’ theory, innovations that are simple, such as EPICS, are often adopted more rapidly and lead to a higher degree of sustainability. Diffusion of Innovations Theory addresses the process of adoption and uptake of interventions by a targeted audience. Three key components of this theory make it well-suited to facilitate adoption of EPICS at the cluster and setting levels. Research suggests that the most effective communication strategy is face-to-face exchange [15]. We hypothesized that social support theory, which uses informal communication channels, helped explain the success of EPICS.

We will continue to use informal communication channels (as recommended by Rogers) to reach change agents and early adopters. Change agents are organizations connected to early adopters*,* organizations that will attempt EPICS before other organizations [15]. Rogers’ theory will provide valuable insights into why EPICS is adopted by some NBLIC community coalitions and not by others. In the EPICS cRCT, this theory will:

1. Explain variance in adoption rates: All clusters will complete Barriers and Enablers to Uptake Assessment (which include setting level-specific questions) to measure key attributes.

2. Explore the impact of facilitators on EPICS dissemination: We will compare key attributes and facilitator knowledge, attitudes and confidence (Pre and Post-Facilitator Training Knowledge, Attitudes and Confidence survey).

3. Evaluate fidelity of implementation to determine adherence to EPICS core elements.

4. Examine the relationship between adoption and outcomes: (*e.g.*, cost-effectiveness analysis, CRC screening rates and number of individuals completing all three EPICS sessions).

5. Establish the role of TA*:* Comparing passive and active arms (providing reinforcement and positive feedback in Rogers’ confirmation stage).

RE-AIM is a framework developed by Glasgow *et al.* designed to evaluate interventions that change health behavior [16]. It has been applied to dissemination studies of various behavioral modification interventions, including a smokeless tobacco intervention [17], diabetes self-management programs [18], smoking cessation [19], physical activity [20], and worksite health behavior interventions [21], as well as interventions in churches [22] and schools [23]. The RE-AIM model is intended to refocus priorities on public health issues and provide balanced emphasis on internal and external validity. Glasgow also concluded that simple and flexible interventions that can be implemented by non-researchers have the greatest potential for long-term maintenance.

RE-AIM is a good tool for evaluating the dissemination of interventions like EPICS, which have the potential to reach a large audience, can be broadly adopted, and can be implemented by different types of staff without a heavy investment of resources [16].

### Primary outcome measures

The primary outcome for the EPICS cRCT focuses on the Reach and Effectiveness components of the RE-AIM (Reach, Effectiveness, Approach, Implementation, Maintenance) model. Reach refers to the proportion of representative eligible organizations, settings, and individuals participating in the intervention. To determine EPICS Reach, we will examine two dimensions of this concept, estimated based on the following calculation [24]:

Number of participants in

$$\text{Estimate}\;\text{of}\;\text{REACH}=\frac{\text{the}\;\text{target}\;\text{population}\;\text{who}\;\text{receive}\;\text{the}\;\text{three}\;\text{EPICS}\;\text{sessions}\;\times \;100}{\text{Number}\;\text{of}\;\text{eligible}\;\text{participants}\;\text{in}\;\text{the}\;\text{target}\;\text{settings}}$$

In the RE-AIM framework, effectiveness is the impact of the intervention on desired outcomes. For the EPICS cRCT, CRC screening adherence will be based on baseline community CRC screening rates from the Centers for Disease Control and Prevention’s (CDC) Behavioral Risk Factor Surveillance System (BRFSS), post intervention participant self-reported FOBT, flexible sigmoidoscopy and/or colonoscopy, and changes in facilitators’ CRC knowledge, attitudes, and beliefs. Adherence to CRC screening on a total population basis is calculated as:

Number of participants

$$\text{Adherence}\;\text{to}\;\text{CRC}\;\text{screening}=\frac{\text{adherent}\;\text{to}\;\text{CRC}\;\text{screening}\;\text{in}\;\text{the}\;\text{population}}{\text{Estimated}\;\text{target}\;\text{population}\;\text{by}\;\text{setting}}$$

In alignment with Glasgow’s RE-AIM definition, our estimate of effectiveness will be determined using the following formula [24]:

Number of participants in the sample of the target population

$$\text{Estimate}\;\text{of}\;\text{Effectiveness}=\frac{\text{who}\;\text{were}\;\text{Reached}\;\text{and}\;\text{adherent}\;\text{to}\;\text{CRC}\;\text{screening}}{\text{Number}\;\text{of}\;\text{participants}\;\text{in}\;\text{the}\;\text{target}\;\text{population}\;\text{who}\;\text{were}\;\text{reached}}$$

### Secondary outcome measures

Qualitative and quantitative research methods are useful in gaining insight and understanding of human behavior, and are recommended by Rogers to study the process of an innovation’s adoption. The secondary outcome for the EPICS cRCT is the percentage of clusters and settings implementing the EPICS sessions. In the RE-AIM framework, adoption is concerned with the representativeness of both the setting in which an intervention is conducted and the change agents who deliver the intervention. EPICS implementation is concerned with quality and consistency of the intervention delivery. It refers to the extent to which various components of an intervention are delivered as intended in real-world settings.

The final RE-AIM dimension, maintenance, refers to the extent to which a program or policy becomes institutionalized or part of the routine organizational practices and policies. At the individual level, measuring maintenance requires follow-up contact six-months or more post-intervention. Due to the timing of CRC screening recommendations (*e.g.*, one to ten years), we will not measure individual maintenance, but will focus at the change agent or cluster level, measuring long-term institutional effects. Organizational impact will be measured based on the following calculation, where fidelity is scored 1 to 4 according to the core elements listed in Table 1:

$$\text{Estimate}\;\text{of}\;\text{Impact}=\frac{\%\;\text{clusters}\;\text{adopting}x\%\;\text{implementing}\;\text{x}\%\;\text{institutionalizing}\;\text{EPICS}}{\text{fidelity}\;\text{to}\;\text{core}\;\text{elements}}$$

**Table 1 T1:** EPICS sessions

**#**	**Title**	**Content**
**1**	Introduction to EPICS	This session provides a general overview of colorectal cancer (CRC) facts. Definitions and screening guidelines; fecal occult blood test (FOBT), sigmoidoscopy and colonoscopy; costs; insurance coverage
**2**	Colorectal cancer screening, symptoms and diagnosis	Common symptoms explained. Finding the cause of symptoms through CEA assay, biopsy, x-rays, sigmoidoscopy or colonoscopy. Definition of treatment methods (surgery, chemotherapy, radiation therapy, biological therapy) Clinical Trials; Social support; developing a plan; monitoring success; EPICS colorectal cancer screening goals.
**3**	Maintaining healthy habits	This session encourages participants to incorporate healthier cooking and eating habits into their lifestyles. It also focuses on CRC screening as an important health habit. Incorporating these healthier lifestyles may potentially confound the effect of the intervention on CRC use.

Adoption is the percent of NBLIC community coalitions approached for participation who did, in fact, participate. Adjustments for attrition will be made using intent-to-treat analysis*.* Implementation is the average percent and extent to which core elements are implemented as intended. Institutionalization is the extent to which NBLIC community coalitions continue to offer EPICS post-implementation.

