### Cost-effectiveness analysis

The active dissemination strategies used in this project are expected to be more effective in engaging the community to implement EPICS with fidelity and thus more effective in increasing CRC screening rates. However, they will also be more expensive than the passive strategies of dissemination. Therefore, in a cost-effectiveness analysis we will determine whether the increased cost is worth the increased effectiveness. We will compare costs and outcomes of the WA, WA + TA, IP, IP + TA dissemination strategies. The cost-effectiveness analysis will be done from the perspective of a public health agency interested in disseminating EPICS (disseminator). It will thus include costs and benefits of disseminator, community coalitions, and settings. Effectiveness will be measured as described above by the increased adherence to CRC screening. Costs of the dissemination strategies will be collected using the assessment tools described above, plus study records and time logs (for example for costs of web and IP training time of personnel and materials, marketing materials, TA personnel time and expenses). From the NBLIC community coalitions we will collect data on costs incurred to engage community partners. Moreover, via periodic telephone interviews to assess the adherence to EPICS implementation protocol we will also collect information on costs related to recruiting participants and delivering the intervention. Costs of personnel time will be valued using age and gender specific wages as reported by the Bureau of Labor Statistics. Costs and outcomes occurring in year two will be discounted using a 3% discount rate. Costs and outcomes of each dissemination strategy will be compared to first eliminate dominated strategies, *i.e.*, those that are more costly than the next most effective ones. Among those that are not dominated we will calculate Incremental Cost Effectiveness Ratios (ICERs), *i.e.*, the ratio of the costs of each strategy net of those of the next less effective one, by the effectiveness. ICERs will be compared to those of similar interventions to establish cost-effectiveness. In addition, we will obtain measures of efficiency for each strategy, *i.e.*, cost per person screened, cost per community partner engaged, and other similar measures. In sensitivity analyses we will vary inputs of the analysis such as wages of personnel or number of participants per education session, to provide a range of cost-effectiveness values under different assumptions.

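### The organizational impact formula divides by fidelity on a 1–4 scale with no stated direction; if 4 is best, higher fidelity lowers the score

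*Protocol article*

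**What the plan says.** The formula is in the protocol article under Secondary outcome measures, where the text turns to maintenance at the level of the coalition. It is introduced with "Organizational impact will be measured based on the following calculation". The numerator is the percentage of clusters adopting, times the percentage implementing, times the percentage institutionalizing. The denominator is fidelity to the core elements, "where fidelity is scored 1 to 4 according to the core elements listed in Table 1". Neither end of the scale is labelled.

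The same section then defines the numerator terms. Adoption is the share of coalitions approached that took part. For the second term it says: "Implementation is the average percent and extent to which core elements are implemented as intended". Institutionalization is the extent to which coalitions go on offering the programme.

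Table 1, cited as the source of the core elements, is a table of sessions with three rows. The last is "Maintaining healthy habits". No row or column is labelled as a core element.

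Elsewhere fidelity is something to be wanted. The Cost-effectiveness analysis section expects the active strategies to lead communities to "implement EPICS with fidelity and thus more effective in increasing CRC screening rates". The Theoretical framework section links fidelity to adherence to core elements, and the Implementation section speaks of measuring its level.

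**The concern.** An impact measure should rise, or at least not fall, when the programme is delivered more faithfully. Dividing by something called fidelity does the opposite unless the scale is coded so that low numbers are good, and the article does not say that it is. Two analysts following the text could code the scale in opposite directions and reach opposite conclusions about what fidelity does to impact.

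There is also an overlap. The implementation percentage already measures how far core elements are delivered as intended. Dividing by a fidelity score for those elements then cancels some or all of the credit that the numerator has just given.

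At stake is whether the one formula given for organizational impact can be interpreted. The primary outcomes do not use it.

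**Working it through.** The article states no numerical impact score, so there is no figure to reproduce. The check is to evaluate the printed formula.

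**Inputs.** Impact = (A × I × M) / F, where A = proportion adopting, I = proportion implementing, M = proportion institutionalizing, and F = fidelity score 1, 2, 3 or 4 (all from Secondary outcome measures). The article gives no values for A, I or M. For illustration I assume A = 0.80, I = 0.50, M = 0.75, so A × I × M = 0.30. The ratios in step 1 do not depend on these values.

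**Step 1. Numerator fixed, 4 = best.**

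| F | Impact |
|---|---|
| 1 | 0.30 / 1 = 0.300 |
| 2 | 0.30 / 2 = 0.150 |
| 3 | 0.30 / 3 = 0.100 |
| 4 | 0.30 / 4 = 0.075 |

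The best score yields 0.075 / 0.300 = 1/4 of the result at the worst score.

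**Step 2. Implementation rises with fidelity, 4 = best.** The article's definition of implementation makes this likely. With A and M equal, the ratio of impact at F = 4 to impact at F = 1 is (I₄ / 4) / (I₁ / 1). The implementation values below are assumed.

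| I at F = 1 | I at F = 4 | Ratio | Net change |
|---|---|---|---|
| 75% | 100% | 0.333 | 3-fold fall |
| 60% | 90% | 0.375 | 2.7-fold fall |
| 50% | 100% | 0.5 | 2-fold fall |
| 25% | 100% | 1.0 | none |
| 20% | 100% | 1.25 | rise |

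If implementation is exactly proportional to fidelity (I = F/4), the formula reduces to A × M / 4 = 0.80 × 0.75 / 4 = 0.15 at every F. Better delivery then earns nothing.

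Implementation cannot exceed 100%, so there is a limit to how far it can compensate. With A and M equal, F = 4 outscores a lower F only if I₄ / 4 > I_F / F. Since I₄ is at most 1, this needs I_F < F/4: below 25% at F = 1, below 50% at F = 2, below 75% at F = 3.

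**Step 3. Reverse coding, 1 = best.** With the numerator fixed, best fidelity gives 0.300 and worst gives 0.075. There is no inversion. Core-element delivery now enters twice in the same direction: if implementation goes from 50% at the worst score (F = 4) to 100% at the best (F = 1), the ratio is (1.00 / 1) / (0.50 / 4) = 8, of which 2 comes from implementation and 4 from fidelity.

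**Step 4. Fidelity in the numerator as F/4, 4 = best.** With the step 1 inputs: 0.30 × 1/4 = 0.075, 0.30 × 2/4 = 0.150, 0.30 × 3/4 = 0.225, 0.30 × 4/4 = 0.300. The score rises with fidelity.

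**The case against.** The strongest reply is that the inversion depends on an assumption. The article does not say that 4 is best, and if 1 is best the formula points the right way. Anchors for a rating scale are also the kind of detail that a condensed article may leave to a scoring manual. This stands in part: the inversion cannot be asserted as fact. It remains the ordinary reading, because the divisor is named fidelity rather than deviation and the rest of the article treats more fidelity as better. The overlap with implementation is present under either coding.

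A second reply is that delivering more core elements also raises the numerator, so four-fold is not the net effect. This stands in full. Four-fold is the limit with the other terms held fixed.

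Third, a reader might infer that the formula ranks the four arms wrongly and penalises the active ones, or that it is the trial's summary of public health impact under the third aim. The document does not support either inference. It never says that the score is computed or compared by arm; the hypotheses, power analysis, cost-effectiveness analysis and RE-AIM analysis sections do not use it; and the third aim is not tied to it. Nor is it a score for a single coalition, because its first term is a percentage of clusters.

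Fourth, a reader might see a contradiction between a scale of 1 to 4 and three sessions. There need be none, since a four-point rating can be applied to three sessions. What remains is only that the article does not say how the score is obtained from Table 1.

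**Conclusion.** The point holds in limited form. As printed, the formula divides by fidelity on a scale whose direction is not given. If a higher score means higher fidelity, greater fidelity lowers the impact estimate, by up to four-fold between scores 1 and 4 with adoption, implementation and institutionalization held fixed. That conflicts with the favourable view of fidelity in the Cost-effectiveness analysis section. Because implementation is defined by delivery of the same core elements, the net change may be a smaller fall, nil or a rise, depending on how strongly implementation moves with fidelity. If 1 is best, the direction is right but delivery is counted twice.

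Severity is minor to moderate. The score is a descriptive composite. Its components are defined separately and assessed separately in the Adoption, Implementation and Maintenance sections, and the primary Reach and Effectiveness outcomes are untouched.

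**What to change.** 1. Either move fidelity to the numerator as a fraction of its maximum (score divided by 4), with the highest score meaning full fidelity, or drop it from the formula because implementation already carries it. If the division is kept, the minimum is to state that 1 is the best score; this settles the direction but not the double counting.
2. Count core-element delivery once. If fidelity stays, implementation needs a definition that does not repeat it. That definition should not simply become the share of coalitions delivering the sessions, because the Adoption section already defines the adoption rate as the share of trained coalitions that implement the programme. The overlap would then move from fidelity to adoption.
3. State how the 1-to-4 score is derived from the three sessions in Table 1, and what each level means.

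The cost is one formula line and its definitions. On the present description no new data are needed, and the composite can be recalculated from its components at any time.
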